## Abstract

**Background:**

Atrial fibrillation (AF) is known to be associated with several pathophysiological mechanisms including endothelial dysfunction of the heart and arterial vessels. Recent evidence suggests that new oral anticoagulant (NOAC) treatment may improve endothelial function and the inflammatory process involved in atherosclerosis in AF patients. This study is designed to determine the efficacy of NOAC therapy in the prevention of endothelial dysfunction and the progression of atherosclerosis of AF subjects.

**Method/design:**

AF patients with a CHA2DS2-VASc score >2 and no previous history of overt coronary disease, severe peripheral arterial disease (PAD) or major stroke will be registered and randomly assigned either to the NOAC group (dabigatran or rivaroxaban) or the warfarin group in this prospective, randomized, 2-year follow-up study. Reactive hyperemia peripheral arterial tonometry (RH-PAT) measurements reflecting endothelial function will be conducted using the Endo-PAT2000 device. Left and right carotid intima-media thickness (IMT) will be measured at baseline, 12 months, and 24 months. The primary endpoint is defined as change in Reactive Hyperemia Index (RHI) at 12 months. Secondary endpoints included changes in the right and left maximum IMT of the common carotid artery (CCA) and internal carotid artery (ICA), the mean IMT of the CCA and ICA at 24 months, and 24-month cardiovascular events including cardiac death, stroke, acute myocardial infarction (AMI), overall cause of death, withdrawal of drug, or bleeding events.

**Discussion:**

This is the first study to evaluate the efficacy of NOAC therapy for the prevention of endothelial dysfunction and progression of atherosclerosis in AF subjects. These findings are expected to expand the knowledge of NOAC pleotropic action in AF patients.

**Trial registration:**

ClinicalTrials.gov: NCT02544932, registered on 7 September 2015.

## Background

Factor Xa and thrombin are well-known components of the coagulation cascade and other biological and pathophysiological processes that are known targets for effective anticoagulation treatment [1]. Therefore, the properties of oral, direct inhibitors of factor Xa (e.g., rivaroxaban) and thrombin (e.g., dabigatran) have been examined for hemostasis and thromboembolism management.

Accumulating evidence suggests that factor Xa and thrombin are important modulators of other cellular signaling mechanisms through the activation of protease-activated receptor (PAR)-mediated signaling. Cross-talk between coagulation and inflammatory pathways via thrombin- or factor Xa-mediated PAR activation on the arterial vessel wall and heart, and the resulting contribution to atherosclerosis and atrial fibrillation (AF), have been well-documented [2]. The endothelium, platelets, pro-inflammatory cytokines and chemokines, and several serine proteases (e.g., tissue factor (TF), factor Xa, thrombin), via the activation of PARs, are major points in for the promotion of inflammation and leukocyte migration, which results in the initiation of atherosclerosis [1–4].

Preclinical studies have provided evidence for the effects of direct Xa or thrombin inhibition beyond anticoagulation, including anti-inflammatory and protective activities in atherosclerotic plaque development [5–8]. Evidence has demonstrated that direct thrombin inhibition impairs the formation and size of atherosclerotic plaques in addition to preventing the progression of endothelial injury-associated stenosis in an apolipoprotein E-deficient mouse model [5, 6]. Also, factor Xa inhibition was shown to ensure the reduction of restenosis after balloon angioplasty of atherosclerotic femoral arteries in rabbits [7].

However, questions remain regarding the treatment concentration and adverse effects of these drugs. Furthermore, there is little evidence of similar effects in patients with AF. Therefore, this study will evaluate the protective effects of NOAC with reactive hyperemia peripheral arterial tonometry (RH-PAT) measurements made using the Endo-PAT2000 device, reflecting endothelial function and intima-media thickness (IMT) of the common carotid artery (CCA), which is used as a surrogate endpoint of atherosclerosis. In this study, we plan to analyze the occurrence of cardiovascular events in AF patients who are at high risk of these.

## Method/design

### Study subjects and hypothesis

Rivaroxaban and dabigatran have demonstrated potential for the management of thromboembolic disorders such as AF or deep vein thrombosis with or without pulmonary thromboembolism [9, 10]. We therefore plan to initiate a prospective, randomized, 2-year follow-up study to clarify the efficacy of rivaroxaban and dabigatran in affecting change of endothelial function and progression of atherosclerosis in AF patients. The working hypothesis of this trial is that rivaroxaban and dabigatran are superior to standard vitamin K (vitK)-antagonists in the prevention of endothelial dysfunction, assessed by peripheral arterial tone (PAT) ratio at 12 months, and the progression of CCA-IMT at 12-month and 24-month follow-up.

### Study design

This study is a prospective, randomized, 2-year follow-up study to clarify the efficacy of rivaroxaban and dabigatran in change of endothelial function and progression of atherosclerosis in AF patients. The study algorithm is shown in Fig. 1. After enrollment, subjects will be randomly assigned to the dabigatran group (110 mg or 150 mg twice/day; group 1) or the rivaroxaban group (20 mg/day; group 2) or the warfarin group (controlled by international normalized ratio (INR) of 2–3; group 3). After participation in the study procedure, clinical follow-up will occur at 1, 3, 12, and 24 months. Follow-up will be conducted via telephone interviews or office visits. Any adverse reactions will be assessed. This study is an investigator-initiated clinical trial with grant support from the Ministry of Health, Welfare, and Family Affairs of the Republic of Korea. The authors are solely responsible for the design, conduct, analysis, and manuscript preparation for this study. The 2-year duration of the study period will have a registration period from September 2015 to February 2016, with complete study duration from September 2015 to April 2018.

**Fig. 1 Fig1:**
[figure not shown]
PREFER-AF trial flow diagram. Participants will receive new oral anticoagulant (NOAC) or vitamin K (vitK)-antagonist treatment according to the assigned sequence; then, endothelial function and clinical events will be assessed

### Study population

Patients aged between 40 to 85 years will be enrolled in the study if they have been diagnosed with AF and have a CHA_2_DS_2_-VASc score above 2 points (Table 1). The following exclusion criteria have been set: severe peripheral arterial disease (PAD) (greater than a Fontaine IIb category), grade-4 or higher cerebral infarction on the modified Rankin Scale, and proven coronary artery disease based on coronary angiogram. In addition, patients with a range of concomitant comorbidities including severe hepatic or renal dysfunction, uncontrolled congestive heart failure, uncontrolled hypertension or diabetes mellitus, hematological disorders, or those with allergy or hypersensitivity to the investigational drugs, pregnant or lactating women, or women wishing to become pregnant, will be excluded. Written informed consent will be obtained from all patients, and the Ethics Review Board of Kyung Hee University Hospital will review the study.

**Table 1 Tab1:** Enrollment criteria

Inclusion criteria	
1. AF (CHA_2_DS_2_-VASc score >2 points)	
2. Aged between 40 and 85 years	
Exclusion criteria	
1. Aged below 40 or over 85 years	
2. History of myocardial infarction	
3. Proven coronary artery disease by coronary angiogram	
4. Cerebrovascular disorders rated as grade 4 or greater on the modified Rankin Scale	
5. Severe peripheral arterial disease rated as Fontaine IIb or over	
6. Uncontrolled hypertension (180/110 mmHg) or diabetes (glycated hemoglobin: HbA1C >10.0 %)	
7. Severe hepatic dysfunction (aspartate transaminase (AST)/alanine transaminase (ALT) >100 mg/dL)	
8. Renal dysfunction (serum creatinine ≥2.0 mg/dL)	
9. Uncontrolled congestive heart failure	
10. Severe hematological abnormalities	
11. Drug allergies or history of hypersensitivity to the investigational drugs	
12. Pregnant or lactating women, or women who wish to become pregnant	

### Randomization and allocation concealment

Randomization will be performed using a computer-generated random number list with a permuted block design at a 1:1:1 ratio. Adequate allocation blinding will be ensured by the following procedure. After obtaining participant consent, allocation information will be sent to the main investigator at Kyung Hee University hospital by telephone, and allocations will not be known by the participants or enrolling investigators.

### Outcome measures

The primary endpoint is defined as change in the Reactive Hyperemia Index (RHI) at 12 months. Secondary endpoints included changes in the right and left maximum IMT of the CCA and internal carotid artery (ICA), mean IMT of the CCA and ICA at 24 months, and 24-month cardiovascular events including cardiac death, stroke, acute myocardial infarction (AMI), overall cause of death, withdrawal of drug, or bleeding events.

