### Sample size measure and statistics

This study is a prospective, pilot study for a proof of concept trial. In a previous studies, the RHI was 1.63 ± 0.28 in patients with permanent/persistent AF [13, 14]. We assume that NOAC will improve RHI values by an 8 % difference with no significant difference between the two different NOACs. The expected difference in RHI was driven from clinical significances and previous medical treatments in other study population [16–18]. To detect a statistically significant difference with a power of 80 % with a two-sided *α*-level of 0.05, a sample of 165 patients (55 patients for each group) will be required. Assuming dropout rates would be 20 %, the total sample size will be set at 198 subjects.

Statistical analyses will be carried out using the SPSS Statistics for Windows ver. 17.0 software package (SPSS Inc., Chicago, IL, USA). A two-sided *p* < 0.05 is considered significant. Continuous variables, presented as means ± standard deviations, will be evaluated for normal distribution and compared using the Student *t* test or analysis of variance test accordingly. The continuous parameters with a skewed distribution will be logarithmically transformed and categorical variables, presented as frequencies and percentages, will be compared using the chi-square test or Fisher’s exact test when appropriate. Repeated measures parameters over time between the groups will be determined by repeated measure analysis of variance with an autoregressive model or analysis of covariance adjusting for baseline values. The clinical event rates will be assessed using the Kaplan-Meier method and the log-rank test will be used to compare survival between the two groups and the Cox proportional hazards model will be used for multivariate analysis (forward stepwise) to investigate which of the parameters identified using univariate analysis are significantly associated with clinical events.

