## Discussion

The aim of this study is to determine the efficacy of NOAC therapy in the prevention of endothelial dysfunction and progression of atherosclerosis in AF subjects. Recent evidence suggests that AF adversely affects endothelial function [11, 13, 14]. Further, conversion of AF to sinus rhythm results in improved flow-mediated vasodilatation (FMD) in patients with persistent AF [13, 14]. It is not known whether the vitK antagonists are effective in affecting endothelial function and atherosclerotic progression in AF patients. Preclinical evidence shows that NOACs are effective in reducing inflammatory cytokines and atherosclerotic cascades [5–8]; however, clinical data are lacking. We believe that the therapeutic effects resulting from aspirin or warfarin and NOACs, which have different mechanisms of action, have not been sufficiently investigated in AF patients. The results of this study are expected to broaden our understanding of NOAC mechanisms in humans and lead to the development of appropriate drug therapies for patients with AF and atherosclerosis. This is a very important objective because the incidence of AF and its common complications are rising at a staggering rate in many countries.

One of the study limitations is that the primary outcome in this study is not a hard endpoint for clinical outcome but a surrogate marker for endothelial dysfunction. Therefore, further study for clinical outcome of vascular events comparing NOACs and warfarin should follow after this trial. Furthermore, this study is not double-blind trial. To minimize the bias, the technician performing examination and analysis will be blind to the allocation of patients.

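### Drug withdrawal, bleeding and all-cause death sit under the label of cardiovascular events and share one survival analysis, so the result may say little about cardiovascular effect

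*Protocol article*

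**What the plan says.** The Outcome measures section, and the Abstract in the same words, lists among the secondary endpoints "24-month cardiovascular events including cardiac death, stroke, acute myocardial infarction (AMI), overall cause of death, withdrawal of drug, or bleeding events". The Background gives the purpose of looking at events: "we plan to analyze the occurrence of cardiovascular events in AF patients who are at high risk of these".

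The section on sample size and statistics has one sentence on how events are analysed. It begins "The clinical event rates will be assessed using the Kaplan-Meier method and the log-rank test will be used to compare survival between the two groups". Its remainder turns to a forward stepwise Cox model for factors associated with clinical events. It does not restrict the event set to cardiovascular items, and it names no analysis by component.

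On blinding, the Discussion says "this study is not double-blind trial" and adds that the technician who examines and analyses is kept unaware of allocation. Under Study design, warfarin is managed to an INR target, whereas no such target is given for the two NOACs.

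**The concern.** Three of the six items are not cardiovascular outcomes, or not only that. Withdrawal of drug is a treatment decision. Bleeding is a safety outcome of anticoagulation and can move in the opposite direction to stroke or AMI. All-cause death adds non-cardiac deaths.

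If all six feed one time-to-event comparison, a difference between NOAC and warfarin could come from any of them. Fewer discontinuations in one arm could look like cardiovascular benefit. A real cardiovascular difference could be hidden, or its direction reversed, by withdrawals or bleeds going the other way. The Cox model would have the same weakness: it might mainly identify predictors of stopping a drug or of bleeding. In either case the result would not serve the purpose stated in the Background.

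Withdrawal is also the item most exposed to bias, because knowing which drug a patient takes can influence the decision to stop it.

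**Working it through.** **The plan's own figures.** The article states no event rate, event count, hazard ratio or power for this endpoint. Its only sample-size figure concerns RHI. With SD 0.28, a difference of 0.08 × 1.63 = 0.1304, two-sided α 0.05, 80% power and two NOAC patients per warfarin patient, the warfarin arm needs 1.5 × (1.960 + 0.842)² × 0.28² / 0.1304² ≈ 54.3, so 55. The total is 55 + 110 = 165, as stated. The figure does not bear on the event endpoint, but it suggests that the two groups in the log-rank sentence are pooled NOAC and warfarin.

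**Is it one endpoint?** Two features point that way: the items stand under one label joined by a final *or*, and one sentence covers the event analysis. No sentence says that the items are analysed separately.

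**How much of it would be cardiovascular?** All rates here are assumptions. Take 24-month risks of 3-10% for cardiac death, stroke or AMI, 10-30% for withdrawal and 5-10% for bleeding, with constant and independent hazards. Each cumulative hazard is H = −ln(1 − risk), and the cardiovascular share is H_cv / (H_cv + H_w + H_b).

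| Assumed risks (CV / withdrawal / bleeding) | H_cv | H_w | H_b | CV share |
|---|---|---|---|---|
| 3% / 30% / 10% (lowest) | 0.030 | 0.357 | 0.105 | 6% |
| 6% / 20% / 5% (middle) | 0.062 | 0.223 | 0.051 | 18% |
| 10% / 10% / 5% (highest) | 0.105 | 0.105 | 0.051 | 40% |

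Non-cardiac deaths are left out; including them would lower the share further.

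In patients, the middle row gives a composite risk of 1 − 0.94 × 0.80 × 0.95 = 0.286. That is about 57 of 198 with a first event, while 198 × 0.06 ≈ 12 would have a cardiovascular event.

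**What could the comparison show?** Use the middle row with bleeding HR 1.0. The composite HR is (HR_cv × 0.062 + HR_w × 0.223 + 0.051) / 0.336.

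| HR for CV | HR for withdrawal | Composite HR | Appearance |
|---|---|---|---|
| 1.0 | 0.6 | 0.74 | benefit with no cardiovascular effect |
| 0.6 | 1.0 | 0.93 | cardiovascular effect nearly hidden |
| 0.6 | 1.5 | 1.26 | direction reversed |

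The hazard ratios are also assumed. The table shows what can happen, not what is expected.

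**The case against.** The strongest reply is that the article never says the items are pooled. It uses neither composite nor time to first event, and it speaks of event rates in the plural. The same run-on sentence lists several IMT measures that nobody would merge into one variable. Naming cardiac death beside all-cause death is odd in a composite but ordinary in a list of outcomes reported one by one. If separate tests were intended, the cardiovascular items could be read on their own. This stands as a real ambiguity, and it rules out saying flatly that the event result cannot be interpreted. It does not remove the problem, because withdrawal and bleeding would still be labelled cardiovascular and the text gives no separate analysis.

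A second reply is that the article does not say who decides on withdrawal or what that person knows. The section on allocation concealment says that neither participants nor enrolling investigators will know the allocation. That statement concerns assignment. Given the Discussion's statement on blinding and the INR-managed warfarin arm, it is not evidence of blinded treatment. Bias in withdrawal is therefore a possibility that the design leaves open; it has not been shown.

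A third reply is that this is a secondary endpoint in a self-described pilot sized for RHI, and that the Discussion defers clinical outcomes to later work. That is correct, and it limits the consequence.

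**Conclusion.** The point holds as a fault in how the endpoint is defined. Read in the most natural way, the planned event analysis mixes cardiovascular outcomes with withdrawal, bleeding and non-cardiac death, and its result could be driven by those. Under the assumed ranges the cardiovascular components contribute roughly 6-40% of the hazard. That range depends wholly on the assumed risks, constant independent hazards and the single-endpoint reading.

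A reader might infer three stronger things that the article does not support:

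- **That withdrawals and bleeds will certainly dominate, by a known margin.** No rates are given, so no narrow figure can be defended.
- **That deaths are counted twice.** In a time-to-first-event analysis a cardiac death counts once. The overlap with all-cause death is only a redundancy, and it would matter only if events were summed.
- **That follow-up for events stops at drug withdrawal.** No such censoring rule is stated.

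The change should be made, but the primary conclusion on RHI does not depend on it.

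**What to change.** Reword the endpoint in Outcome measures and in the Abstract:

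- **Cardiovascular composite:** cardiac death, stroke or AMI, time to first event.
- **All-cause death:** a separate outcome.
- **Bleeding:** a safety outcome.
- **Drug withdrawal:** a tolerability outcome.

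State in the statistics section that the Kaplan-Meier, log-rank and Cox analyses are applied to each of these separately.

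All the items are already listed as outcomes, so only wording changes. The cost is precision: under the assumed 3-10% risk, the cardiovascular composite would have about 6 to 20 events among 198 patients (198 × 0.03 to 198 × 0.10). For an assumed HR of 0.6 with two NOAC patients per warfarin patient, the Schoenfeld formula asks for (1.960 + 0.842)² / (2/3 × 1/3 × (ln 0.6)²) ≈ 136 events for 80% power. With 6, 12 or 20 events the power is about 9%, 13% or 19%. Intervals will therefore be wide, and the cardiovascular result will be largely descriptive.

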### Procedures

Measurement of PAT ratio will be performed with the standard technique and device [11–14]. Endo-PAT measurements will be performed at baseline and at 12 months after randomization. The RH-PAT 2000 device (Itamar Medical, Caesarea, Israel) will be used for digital RH-PAT to evaluate endothelial function as previously described. The RH-PAT Index (RHI) reflects the extent of reactive hyperemia and is calculated as the ratio of the average amplitude of PAT signal over 1 min starting 1.5 min after cuff deflation (control arm, A; occluded arm, C) divided by the average amplitude of PAT signal at the 2.5-min time period before cuff inflation (baseline) (control arm, B; occluded arm, D). Thus:$$ RHI = \left(C/D\right)/\left(A/B\right) \times \mathrm{baseline}\ \mathrm{correction}. $$

Impaired endothelial function is defined as a log RHI less than 0.6, and favorable endothelial function is defined as a log RHI more than or equal to 0.6.

Measurement of CCA-IMT will be performed with the standard technique and device [12, 15]. Imaging studies of the left and right carotid arteries will be performed by expert sonographers who are well-trained in the use of 10-MHz linear vascular probes (Vivid 7, GE Vingmed Ultrasound, Horten, Norway). Measurements will be performed at baseline, and at 12 months and 24 months after randomization. To avoid interobserver variability, the same investigator will examine each participant with the same equipment throughout all the visits. The IMT will be measured as the distance between two parallel echogenic lines corresponding to the blood-intima and media-adventitia interface on the posterior wall of the artery. Three IMT determinations will be performed at the site of the thickest point with a maximum CCA-IMT and two adjacent points (1 cm upstream and 1 cm downstream from this site). These three determinations will be averaged (mean CCA-IMT). The CCA is defined as the segment extending from 10 to 20 mm proximal to the tip of the common carotid bifurcation site. The ICA is defined as the segment 10 mm distal to the tip of the common carotid bifurcation site, and the bifurcation is defined as the segment between the CCA and the ICA. Carotid IMT will be measured using dedicated software (Intimascope, Media Cross Co., Tokyo, Japan) by an examiner blinded to all clinical information.

Blood samples will be obtained from subjects in the fasting state. The von Willebrand factor, interleukin (IL)-10, and adiponectin endothelial cell markers, the IL-6, tumor necrosis factor alpha (TNF-α), and high-sensitivity C-reactive protein (hs-CRP) inflammatory markers, the vascular adhesion molecule and ICAM-1 adhesion molecules, and the CD-40 ligand, P-selectin, and cathepsin-K platelet activation markers will be measured using standard methods.

### Sample size measure and statistics

This study is a prospective, pilot study for a proof of concept trial. In a previous studies, the RHI was 1.63 ± 0.28 in patients with permanent/persistent AF [13, 14]. We assume that NOAC will improve RHI values by an 8 % difference with no significant difference between the two different NOACs. The expected difference in RHI was driven from clinical significances and previous medical treatments in other study population [16–18]. To detect a statistically significant difference with a power of 80 % with a two-sided *α*-level of 0.05, a sample of 165 patients (55 patients for each group) will be required. Assuming dropout rates would be 20 %, the total sample size will be set at 198 subjects.

Statistical analyses will be carried out using the SPSS Statistics for Windows ver. 17.0 software package (SPSS Inc., Chicago, IL, USA). A two-sided *p* < 0.05 is considered significant. Continuous variables, presented as means ± standard deviations, will be evaluated for normal distribution and compared using the Student *t* test or analysis of variance test accordingly. The continuous parameters with a skewed distribution will be logarithmically transformed and categorical variables, presented as frequencies and percentages, will be compared using the chi-square test or Fisher’s exact test when appropriate. Repeated measures parameters over time between the groups will be determined by repeated measure analysis of variance with an autoregressive model or analysis of covariance adjusting for baseline values. The clinical event rates will be assessed using the Kaplan-Meier method and the log-rank test will be used to compare survival between the two groups and the Cox proportional hazards model will be used for multivariate analysis (forward stepwise) to investigate which of the parameters identified using univariate analysis are significantly associated with clinical events.

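### The 20% dropout allowance multiplies 165 by 1.2 instead of dividing by 0.8, so 198 patients leave about 158 evaluable and pooled power of about 78%, not the stated 80%

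*Protocol article*

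**What the plan says.** The calculation is in the protocol article, under Sample size measure and statistics. It takes a reference value from earlier studies, "the RHI was 1.63 ± 0.28 in patients with permanent/persistent AF", and an expected effect, "We assume that NOAC will improve RHI values by an 8 % difference", "with no significant difference between the two different NOACs". With 80% power and "a two-sided *α*-level of 0.05", it concludes that "a sample of 165 patients (55 patients for each group) will be required". The next sentence adds the allowance for loss: "Assuming dropout rates would be 20 %, the total sample size will be set at 198 subjects".

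Under Randomization and allocation concealment, patients are allocated "with a permuted block design at a 1:1:1 ratio", so 198 means 66 per group. Under Outcome measures, the primary endpoint is the change in RHI at 12 months. Under Procedures, the Endo-PAT measurement is made only at baseline and at 12 months. The article gives no inflation formula and does not say that patients who drop out will still supply a 12-month RHI.

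**The concern.** Two adjacent sentences do not agree. The first fixes the number needed for the stated power at 165. The second sets an enrolment total that falls below 165 once the assumed 20% is removed. The total looks like the required number raised by 20%, which is a different operation from finding the number that leaves 165 after 20% of those enrolled are lost.

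The total of 198 is the recruitment target, and the Trial status section says enrolment is under way. If it is wrong, the trial can meet its target, lose exactly the proportion it planned for, and still have fewer evaluable patients than its own calculation requires. There is no intermediate RHI measurement, so a patient lost before 12 months contributes no post-baseline value to the primary comparison.

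**Working it through.** **Inputs**, all from Sample size measure and statistics except the allocation ratio, which is from Randomization and allocation concealment:

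- two-sided α = 0.05, power 0.80
- reference mean 1.63, SD 0.28
- effect 8% of 1.63 = 0.1304, so d = 0.1304 / 0.28 = 0.4657
- allocation 1:1:1, with the two NOAC arms assumed equal
- required sample 165, dropout 20%, total 198

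**Step 1: reproduce the plan's 165.** Pool the two NOAC arms against warfarin (2:1). The number of controls is

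n = (1 + 1/2) × [SD × (z₀.₉₇₅ + z₀.₈₀) / Δ]² = 1.5 × [0.28 × (1.960 + 0.842) / 0.1304]² = 54.3, rounded up to 55.

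That gives 55 warfarin and 110 NOAC patients, 165 in all, an exact match. Other readings do not match: a 1:1 comparison of one NOAC with warfarin needs 73 per group two-sided or 58 per group one-sided, and a three-group ANOVA with 55 per group has 70.6% power.

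**Step 2: reproduce the plan's 198.** 165 × 1.20 = 198. This is the operation that gives the stated total.

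**Step 3: apply the dropout rate to those enrolled.** The total N must satisfy N × (1 − 0.20) ≥ 165, so N ≥ 165 / 0.80 = 206.25. Rounded up, N = 207, or 69 per group. Check: 207 × 0.80 = 165.6. The stated total is 207 − 198 = 9 too low (9 / 207 = 4.3%).

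**Step 4: what 198 delivers.**

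- Evaluable at 20% dropout: 198 × 0.80 = 158.4, or 52.8 per group, a shortfall of 165 − 158.4 = 6.6.
- Largest dropout that still leaves 165: 1 − 165/198 = 16.7%.

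**Step 5: power**, by the noncentral t distribution with d = 0.4657, pooled NOAC against warfarin:

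| Case | NOAC vs warfarin | Power |
|---|---|---|
| Required number | 110 vs 55 | 80.1% |
| 198 enrolled, 20% lost | 105.6 vs 52.8 | 78.4% |
| 207 enrolled, 20% lost | 110.4 vs 55.2 | 80.2% |

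The normal approximation gives 80.5% and 78.9% for the first two rows. The base number has almost no slack, so any shortfall takes power below 80%.

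Other readings for comparison: one NOAC against warfarin falls from 67.7% (55 vs 55) to 65.9% (52.8 vs 52.8), and the three-group ANOVA falls from 70.6% to 68.7%. In both, the dropout step costs about 2 points. The rest of the deficit is already present at 55 per group.

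**The case against.** The arithmetic itself is hard to dispute. The case on the other side concerns how much it matters.

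- **Size.** On the reading that reproduces 165, the loss is about 1.6 points, in a study that calls itself a pilot with a surrogate endpoint. This stands: it is not serious underpowering and would hardly change what the trial can conclude.
- **Pairwise power.** The figure of 65.9% for a single NOAC comes mainly from the base calculation, which would need 73 per group for that comparison. This also stands. It is a separate matter, and only the last 1.8 points belong here.
- **Timing.** The article does not say whether 20% is the loss by 12 or by 24 months. If it is the 24-month figure, and no more than 16.7% are lost by 12 months, 198 would still leave 165 for the primary endpoint. That is possible, but nothing in the article says so, and the allowance directly follows the power calculation.
- **Covariate adjustment.** The statistics paragraph permits analysis of covariance on baseline. Since 158.4 / 165 = 0.96 and the variance factor is 1 − r², a baseline-to-12-month correlation of about 0.2 would offset the shortfall. The article gives no such correlation and does not use one in the calculation. An unadjusted change-score analysis would not benefit in this way.

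The last two points show how modest the shortfall is. Neither makes 198 the right allowance for 20% dropout.

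**Conclusion.** The concern holds. The total of 198 comes from the wrong operation; 20% dropout requires 207. As written, 198 leaves about 158 evaluable patients, tolerates 16.7% loss, and gives about 78.4% power for the pooled comparison instead of 80%. The consequence is small, but the figure is the recruitment target and the statement attached to it is untrue.

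The conclusion rests on three assumptions: the 20% is lost before the 12-month RHI, those patients provide no primary outcome, and power is calculated on the plan's own inputs (SD 0.28, difference 0.1304, NOAC arms pooled). The error in the enrolment total itself does not depend on the power model. It follows from 165, 20% and 198 alone.

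**What to change.** Correct the dropout sentence in one of two ways.

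1. **Keep 198 and restate what it covers.** Say that 198 subjects (66 per group) allow for 16.7% dropout, and that 20% dropout would leave about 158 evaluable with about 78% power for pooled NOAC against warfarin. This costs one sentence and a slightly less favourable claim, with no extra patients.
2. **Keep the 20% allowance and correct the total** to 165 / 0.8 = 206.25, rounded up to 207 (69 per group). This costs nine more patients.

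Either way, the sentence should say that the dropout rate refers to loss before the 12-month RHI measurement, if that is what is meant.
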